### 3.0 Objectives

The primary objectives of the study are to:

1. Evaluate the safety and tolerability of anakinra in children age  $\geq 4$  years with MPS III, defined by the incidence of treatment-emergent adverse events and abnormal laboratory values, and number of subjects withdrawn due to intolerability (e.g. unable to administer SC injection to subject, worsening behaviors).
2. Evaluate the effect of anakinra on a multi-domain responder index (MDRI) as a means to determine need for dose escalation. Due to the inherent heterogeneity of disease presentation, the MDRI will measure change tailored to patient-specific symptoms. MDRI change will inform dose-finding by reflecting lack of change in clinical outcome. The MDRI will be composed of the following:
  - Sanfilippo Behavior Rating Scale (SBRS)
  - Child Sleep Health Questionnaire (CSHQ)
  - Autism Parenting Stress Index (APSI)
  - PROMIS Fatigue - Parent Proxy Custom Short Form
  - Seizures – parent reported frequency, duration, and severity
  - Movement disorder (e.g. dystonia, chorea, etc.) – parent reported frequency, duration, and severity
  - Non-communicating Children's Pain Checklist-Revised (NCCPC-R)

The secondary objectives of the study are to evaluate the effect of anakinra on:

- Individual Clinical Response (ICR) – 5 most impactful clinical problems reported by the caregiver
- Gait
- Stair climb/descent
- Sleep Diary (1-week recall)
- Sanfilippo Syndrome Stool Habit Questionnaire

The exploratory objectives of the study are to evaluate the effect of anakinra on:

- ☐ Stool microbiome
- ☐ Vineland Adaptive Behavior Scales, Third Edition (VABS-III)

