### **6.0 Study-Wide Number of Subjects**

Twenty (20) subjects will be enrolled in this pilot study. Individuals who withdraw before Week +8 will be replaced.

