## 9.0 Study Endpoints

### 9.1 Primary and secondary endpoints.

#### Primary endpoints:

Phase 1: Incidence of treatment-emergent adverse events and laboratory values over 8 weeks of treatment to known frequency of anakinra-related AEs in other populations.

Phase 2: Need for dose escalation as determined by within individual change over 8-week treatment period compared to change over 8-week observational period in the 2 most bothersome symptoms for each enrolled patient, selected from measures for the MDRI. Choices are below in bold. These 2 symptoms will be monitored by one or more of the assessments below. If the Minimal Clinically Important Difference (MCID) that is defined below is not achieved after 8 weeks of treatment, or there has been a decrease of more than the MCID between 8 and 16 weeks after an increase greater than MCID at week 8, the dose will be escalated (see Section 27.7). If the MCID is not achieved after 8 weeks on maximum trial dose of 200mg (max dose 8 mg/kg/day), treatment with anakinra may be discontinued (see Section 27.7).

- Sanfilippo **Behavior** Rating Scale (SBRS): MCID = 0.25 SD for each scale
  - Symptoms described in table below:

|                         |                                                                                                                                        |                           |
|-------------------------|----------------------------------------------------------------------------------------------------------------------------------------|---------------------------|
| Body Movements          | Makes large complex movements of their body, such as spinning, twirling or repeatedly bouncing up and down.                            | Movement                  |
| Object Interaction      | Examines or manipulates some novel or unfamiliar objects repeatedly.                                                                   |                           |
| Activity/Routines       | Never plays with one object or engages in one activity for very long.                                                                  |                           |
| Emotional Function      | Expresses emotions inappropriate to the situation.                                                                                     | Social/emotional function |

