## 12.2 Analysis

### **Primary objective**

Outcome variables include AEs/tolerability, 2 most bothersome symptoms, and multi-domain responders index (MDRI) as described in section 9.1. Binary AEs such as hospitalization ( $\geq 1$ ) will be summarized using frequencies/rates by the two period (pre-observation, treatment). The multiple event such as the total number of seizures will be summarized using median with the inter-quartile range (IRQ). For testing changes between the two periods, the McNemar's test (binary event) or Wilcoxon Signed Rank test (multiple events and MDRI) will be used. For continuous outcomes such as laboratory results, a paired t-test and a repeated measures ANOVA will be used. Residual analyses will be conducted to check the model assumption. If it violates assumption, Friedman test (nonparametric) will be used instead.

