### **Exploratory objective**

Explanatory outcomes include stool microbiome and Vineland 3. The similar analyses as ones for primary and secondary objectives will be carried out based on data types.

Analyses will be conducted using the programs of SAS v9.4 (SAS Institute, Cary, NC). All tests will be two-tailed and a P value less than 0.05 will be considered statistically significant. The primary outcome will be tested at the 5% significance level. Secondary, exploratory and sensitivity analyses will not be adjusted for multiplicity. Therefore, the results will be interpreted with caution and discussed with recognition of inflated family-wise type I error rate.

Descriptive statistics will be provided on all study data collected from the total cohort (N=20) from the entry to the trial to the completion of 44 weeks follow-up continuous variables will be summarized as numbers of observed and missing values, mean, standard deviation, median, minimum and maximum. Categorical variables will be described as frequencies and percentages.

Any post-hoc, exploratory analyses or deviations which were not identified in this data analysis plan but are completed to support the planned analyses will be clearly identified and the reasons documented.

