### **12.3 Power**

The sample size of 20 for the study was determined primarily by feasibility rather than statistical power due to the extremely rare nature of the disease. However, the level of precision in estimation of AEs during the treatment period was computed with a given samples size of 20 using 95% confidence interval. For estimation of the binary event, the margin of the error would be 13% to 18% when the sample proportion are assumed to be 5% to 15%. For continuous outcomes, the margin of the error would be a half fold of the standard deviation in estimation of paired difference between the treatment and first observation period.

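### Laboratory safety is defined as an incidence of abnormal values, but section 12.2 names only tests of mean change for laboratory results

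*Protocol*

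**What the plan says.** Section 3.0 states the first primary objective as safety and tolerability, "defined by the incidence of treatment-emergent adverse events and abnormal laboratory values", together with withdrawals for intolerability. Section 9.1 gives the Phase 1 primary endpoint as "Incidence of treatment-emergent adverse events and laboratory values over 8 weeks of treatment to known frequency of anakinra-related AEs in other populations". Both are statements about incidence, and the second asks for a comparison with an outside frequency.

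Section 12.2, under the primary objective, names laboratory results once: "For continuous outcomes such as laboratory results, a paired t-test and a repeated measures ANOVA will be used". If residual checks fail, a Friedman test replaces these. Later in the same section: "All tests will be two-tailed and a P value less than 0.05 will be considered statistically significant", and "The primary outcome will be tested at the 5% significance level".

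Other provisions touch laboratory data:

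- Section 12.2 promises descriptive statistics on all study data: mean, SD, median, minimum and maximum for continuous variables, frequencies and percentages for categorical ones.
- Section 12.2 summarises binary adverse events as frequencies or rates by period, and section 13.2 treats a laboratory abnormality as an adverse event if it meets any one of five conditions.
- Section 12.3 says the sample size "was determined primarily by feasibility rather than statistical power due to the extremely rare nature of the disease" and then gives 95% confidence-interval margins for adverse events and for paired differences.

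**The concern.** The protocol has not simply left the laboratory analysis open. It fixes a method, and that method is of a different type from the endpoint. An incidence asks how many participants had an abnormal value. A paired t-test or repeated measures ANOVA asks whether the average moved, and the Friedman test asks a similar question of ranks. None of them returns a proportion of participants.

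If section 12.2 were followed literally, the report would give mean changes and p-values for each laboratory parameter but not the quantity that the primary objective names. The comparison required by section 9.1 could not be made for the laboratory part. The protocol itself treats laboratory risk as a matter of individual limits: liver-enzyme limits in section 14.0, cell-count limits in section 27.7 and grade-based stopping rules in section 13.4. A mean is poorly suited to showing such events when they occur in a few participants.

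**Working it through.** **Step 1. Does any stated analysis count participants with an abnormal laboratory value?**

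| Place | What it yields | Counts every participant with an abnormal value? |
|---|---|---|
| 12.2, paired t-test / ANOVA / Friedman | Test of change in mean or rank | No |
| 12.2, descriptives for continuous variables | Mean, SD, median, minimum, maximum | No. The extremes show the worst values, not how many crossed a limit |
| 12.2, descriptives for categorical variables | Frequencies and percentages | Only if laboratory results are classified as abnormal or graded, which the protocol does not say |
| 12.2 adverse-event frequencies, with 13.2 | Abnormalities that meet an adverse-event condition | In part. Section 3.0 lists abnormal values separately from adverse events |

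The adverse-event route also lacks a like-for-like baseline. Before treatment starts, only serious events tied to protocol procedures are recorded (section 10.2, footnote f). Laboratory values are drawn at Screening, Week -8 and Day 1 (section 10.4), so an incidence analysis would have pre-treatment data to work from.

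**Step 2. Reproduce the protocol's own precision figures (section 12.3, n = 20).**

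- Binary: the half-width of the exact (Clopper-Pearson) 95% interval is 12.4% at 1/20 and 17.3% at 3/20. The protocol states 13% to 18% for proportions of 5% to 15%, so it agrees to within about one point.
- Continuous: t(0.975, 19)/√20 = 2.093/4.472 = 0.468 SD of the paired difference. The protocol states about half an SD, which agrees.

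**Step 3. Sensitivity of the mean test (paired t, n = 20, two-sided 5%).** The protocol gives no laboratory SD, so shifts are in units of the SD of the within-patient change. This is an assumption.

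*Everyone shifts by d.* Power comes from the noncentral t with noncentrality d√20: 25% at d = 0.3, 56% at d = 0.5, 72% at d = 0.6 and 92% at d = 0.8. It takes d = 0.66 to reach 80%.

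*Only k of 20 shift, by s SD.* Simulated rejection rates, 40,000 runs each:

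| k of 20 | s = 2 | s = 3 | s = 4 |
|---|---|---|---|
| 1 | 5.0% | 4.7% | 4.1% |
| 2 | 7.6% | 8.5% | 8.2% |
| 3 | 13.0% | 16.2% | 17.7% |
| 4 | 20.1% | 28.8% | 35.0% |

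The rates stay low because large individual changes inflate the SD along with the mean. The mean shift is ks/20, and the expected sample variance is 1 + s²k(20 − k)/380. For k = 3 and s = 4 the mean shift is 0.60 and the variance is 1 + 16 × 51/380 = 3.15, so the SD is 1.77. The typical t is then 0.60 × 4.472/1.77 = 1.51, against a critical value of 2.093. As s grows without limit, t tends to √(19k/(20 − k)), which for k = 3 is √(57/17) = 1.83, still below 2.093.

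These runs cover the paired t-test. The repeated measures ANOVA and the Friedman fallback were not simulated.

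**Step 4. What an incidence summary would show (exact two-sided 95% interval, n = 20).**

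- 0/20: upper limit 1 − 0.025^(1/20) = 16.8%.
- 1/20: 0.1% to 24.9%.
- 3/20: 3.2% to 37.9%.

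The chance of seeing at least one case is 1 − (1 − p)^20: 64% at a true rate of 5%, 88% at 10% and 96% at 15%.

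A significance test of the counts would not do the same job. With no events before treatment, exact McNemar needs 6 new cases of 20 (2 × 0.5⁶ = 0.031; 5 cases give 0.063), so its power is 7% at a true rate of 15%. The uncorrected chi-square version needs 4 cases and has 35% power.

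**The case against.** The best case for the plan is that the t-test is not its detector of individual harm. Descriptive statistics are promised for all data, including the extremes. The more serious abnormalities should reach the adverse-event counts: ALT or AST above 3 times the upper limit triggers repeat testing under section 14.0, which meets the further-tests condition in section 13.2, and persistent low cell counts lead to dose action under section 27.7. Section 12.3 openly sets the sample size by feasibility and frames it as interval precision. Tabulations of abnormal values are also often left to a statistical analysis plan, which may exist.

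Much of this stands, and it bars two stronger readings that a reader might infer. One is that a non-significant laboratory test would be taken as evidence of safety. No section says so: the 5% statement is a general significance level, and the stopping and dose criteria rest on individual values and grades. The other is that the safety plan as a whole misses most harms. The low rejection rates describe the t-test alone, under assumed shifts.

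The mismatch itself is not answered. Section 3.0 lists abnormal laboratory values alongside adverse events, so counting only those that qualify as adverse events gives a subset of the stated endpoint. The argument about a separate analysis plan would carry more weight if section 12.2 were silent. It names a method, and it closes by requiring that analyses it does not identify be flagged as such.

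**Conclusion.** The point holds in this form: for the laboratory part of a primary endpoint defined as an incidence, section 12.2 names only tests of mean or rank change. These cannot estimate the incidence or be compared with a frequency in another population. The descriptives and the adverse-event route cover it in part.

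The mismatch can be read from the text and needs no assumption. The size of the insensitivity, 4% to 18% rejection when 1 to 3 of 20 participants are affected, rests on assumed shifts of 2 to 4 SD and on normally distributed changes of equal spread. It illustrates why the mean test is a poor stand-in for a count. It is not an estimate of what this trial will miss. The matter should be corrected, but it does not affect trial conduct.

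**What to change.** In section 12.2, make the primary laboratory summary the number and percentage of participants with a treatment-emergent abnormal value, relative to pre-treatment values:

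- by laboratory reference range, and by the CTC grade already adopted in section 13.3;
- over 8 weeks for the Phase 1 endpoint, and over 36 weeks for the matching secondary endpoint in section 9.1;
- each with an exact two-sided 95% confidence interval, in keeping with section 12.3.

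State that the comparison with other populations uses these proportions and intervals. Keep the paired t-test and ANOVA of means (with the Friedman fallback) as supportive. If a dose-management limit from section 14.0 or 27.7 is also tabulated, carry over its full wording, including any persistence condition, so that the table does not turn it into a different event.

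The cost is a shift table and a set of exact intervals from samples already scheduled. No visits, tests or clinical rules change. The drawback is a less comfortable figure: with no cases in 20 participants, the report would still show an upper limit of 16.8%.

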### **Secondary objective**

Outcome variables include Individual Clinical Response (ICR, 0~25: sum of the top 5 domains on a 5-point Likert scale), Gait analysis results (improved, no change, worsened), Stair climb/descent (time and quality of improvement), Sleep diary (sum of the number of overnight awakenings, average duration of overnight awakenings, and duration of time for initial sleep onset at bedtime), and Stooling survey results. For univariate analyses, similar statistical tests will be used as ones used for the primary objective, depending on the data type of the outcome for comparing two study periods. For multivariate analyses, mixed effect models (linear for continuous outcomes and non-linear such as multinomial logistic regression for categorical outcomes and Poisson (or Negative Binomial regression model, if over-dispersion is apparent) for count outcomes) will be used using 2-4 different time points (pre-observation, 8, 36 week treatment, post-observation periods) as within subject factor. Covariates such as sex and age will be considered in multivariate models if they are found to be statistically significant in changes of outcomes. Sub-scale analyses will be conducted if changes in the composite score are found to be statistically significant or are reached to a clinically meaningful boundary. We expect to have full data without any missing for all outcomes. However, in case of missing data, two imputation methods, i) last observation forward, ii) multiple imputation assuming missing at random, will be considered.

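### Friedman is the only nonparametric fallback named for continuous outcomes; in a two-period comparison it is just the sign test, so the paired t-test needs its own fallback (minor)

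*Protocol*

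**What the plan says.** Section 12.2 of the protocol, under Primary objective, sets out tests by data type. For changes between the pre-treatment observation period and the treatment period it assigns McNemar's test to binary events. For event counts and the multi-domain index it says "Wilcoxon Signed Rank test (multiple events and MDRI) will be used".

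Continuous outcomes follow: "For continuous outcomes such as laboratory results, a paired t-test and a repeated measures ANOVA will be used". Then comes a check, "Residual analyses will be conducted to check the model assumption", and one consequence, "If it violates assumption, Friedman test (nonparametric) will be used instead". No other nonparametric test is named for continuous outcomes, and neither the check nor the fallback is tied to one of the two parametric tests.

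The Secondary objective text says that for univariate analyses "similar statistical tests will be used as ones used for the primary objective", chosen by data type, when two study periods are compared. The Exploratory objective text extends similar analyses to the stool microbiome and the Vineland-III.

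**The concern.** One fallback follows two parametric tests that need different ones. Friedman is the usual rank counterpart of a repeated-measures ANOVA over three or more occasions. The usual rank counterpart of a paired t-test is the signed-rank test. Read as written, a two-period comparison that fails the residual check could be sent to Friedman, which then keeps only the direction of each child's change.

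That would also be inconsistent within the paragraph: a two-period change in an event count would be analysed by signed-rank, and a two-period change in a continuous measure by what amounts to a sign test, with no reason given. At stake is some efficiency in comparisons based on 20 children: laboratory values, and continuous secondary or exploratory outcomes to the extent that the same tests are carried over to them.

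**Working it through.** **Inputs from the protocol**
- Sample size: "Twenty (20) subjects will be enrolled in this pilot study" (section 6.0).
- Significance rule: "All tests will be two-tailed and a P value less than 0.05 will be considered statistically significant" (section 12.2, Exploratory objective).
- No power, effect size or distribution of paired differences is stated. Section 12.3 bases the sample size on feasibility.

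**Assumptions (not in the protocol)**
- Paired differences are normal, logistic, t with 5 df, t with 3 df, Laplace or uniform.
- Shifts run from 0 to 1.5 SD of the differences, in steps of 0.05.

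**The nearest stated figure.** Section 12.3 gives a margin of error of about half an SD for a paired difference. Check: t(0.975, 19)/√20 = 2.093/4.472 = 0.468 SD. It reproduces and is not in question.

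**Friedman with two periods.** Let S be the number of children, out of n, whose value rises, with no ties. The rank sums are R1 = n + S and R2 = 2n − S. With k = 2,

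Q = [12/(n·2·3)]·(R1² + R2²) − 3n·3 = (2/n)(5n² − 2nS + 2S²) − 9n = (2S − n)²/n.

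This depends on S alone and is the sign-test statistic. At n = 20:
- S = 14: Q = 8²/20 = 3.2, p = 0.074; exact sign test p = 0.115.
- S = 15: Q = 10²/20 = 5.0, p = 0.025; exact sign test p = 0.041.

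Both reject when S ≥ 15 or S ≤ 5, and the attained size is 0.0414. The exact signed-rank test rejects when W ≤ 52 or W ≥ 158, and its attained size is 0.0484.

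**Power.** 200,000 simulated trials were run per distribution, so the Monte Carlo standard error is at most √(0.25/200,000) = 0.0011, about 0.1 point. Each row shows the shift at which the loss is largest.

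| Assumed differences | Shift (SD) | Friedman/sign | Signed-rank | Loss (points) |
|---|---|---|---|---|
| Laplace | 0.60 | 75.7% | 79.7% | 4.0 |
| t, 3 df | 0.40 | 54.0% | 61.1% | 7.1 |
| t, 5 df | 0.55 | 59.6% | 71.4% | 11.8 |
| Logistic | 0.55 | 53.8% | 66.9% | 13.1 |
| Normal | 0.60 | 52.0% | 70.0% | 18.0 |
| Uniform | 0.70 | 42.3% | 76.9% | 34.6 |

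The Friedman column can be checked without simulation. For normal differences at 0.60 SD each child rises with probability Φ(0.60) = 0.7257, and P(S ≥ 15) + P(S ≤ 5) for a binomial with 20 trials is 0.518, against 0.520 simulated.

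In the normal case about 2 of the 18 points come only from the sign test's smaller attained size (0.041 against 0.048). At matched size the loss is about 16 points.

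**Where two-period comparisons arise.** Section 9.1 frames the secondary endpoints partly as change over 8 treated weeks against change over 8 observed weeks, which is two values per child. In the schedule of section 10.2 the Vineland-III is taken only at Week -8 and Week +36, so a Friedman test on it would have exactly two levels. Safety laboratory tests, by contrast, are taken at ten or more time points (sections 10.2 and 10.4), where Friedman fits.

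**The case against.** The strongest reply is that Friedman was meant for the ANOVA alone. The check refers to a model in the singular, residuals belong more naturally to an ANOVA, and the example given is laboratory results, a long series of visits. This reading is plausible and cannot be excluded. For that reason a reader should not conclude that the plan definitely replaces the paired t-test by Friedman; the text does not say so. It does not limit Friedman to the ANOVA either, and on that narrower reading the paired t-test has no fallback at all. Both readings call for the same sentence.

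Second, the carry-over to secondary outcomes is worded loosely (similar tests, by data type), and mixed models over two to four time points are also planned there. Signed-rank is therefore not ruled out for those outcomes, and a firm claim that they inherit Friedman would go too far. This objection stands.

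Third, a reader might take the 18-point figure as the expected or greatest loss. It is neither. It belongs to normal differences, where the assumption holds and the fallback would normally stay unused. The heaviest-tailed shapes tried lose 4 to 7 points, and the uniform shape loses about 35.

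Fourth, matching fallbacks to tests is often left to an SAP. That is fair, but here the protocol names a specific test, and section 12.2 also asks that departures from its analysis plan be identified and justified. If a separate SAP already makes the assignment, the protocol sentence need only be aligned with it.

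**Conclusion.** The point holds as a minor one. The protocol names one fallback after two parametric tests without saying which it serves. If used for a two-period comparison, that fallback is the sign test, which is inconsistent with the signed-rank test used in the same paragraph.

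The maximum loss of power ranges from about 4 to about 35 points across the six symmetric shapes tried, at n = 20 and two-sided 5%. These figures rest on assumed shapes and shifts and are illustrative. With strongly skewed differences the two tests address different quantities, so their power is not directly comparable and no loss is claimed there.

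Wider consequences might be inferred but are not supported. The MDRI already has signed-rank. Dose escalation follows each child's change against the MCID (sections 9.1 and 27.7), not these p-values. No planned power is lost, because none was planned.

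**What to change.** In section 12.2, Primary objective, replace the fallback sentence with one that assigns each test: for two-period comparisons of continuous outcomes, where the paired t-test is planned, the fallback is the Wilcoxon signed-rank test; Friedman replaces the repeated-measures ANOVA only when three or more time points are compared.

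The cost is one sentence, with no change to data collection, visits or sample size. The small downside is that signed-rank assumes roughly symmetric differences, which the sign test does not.
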